## Abstract

**Background:**

Enteral tube feeding provides supplementary or alternative nutrition for individuals who cannot meet their nutritional needs orally and remains essential for a number of children and young people with complex health needs. Commercial formula remains standard practice in the UK, although increasing numbers of children and their families are choosing a blended diet and reporting significant physical and social benefits. However, support for families in using blended diets varies across health, education and social settings in the UK.

**Aim:**

To explore factors affecting the use of blended diets in health, education and social care settings.

**Methods:**

This sequential mixed methods study uses a realist approach to understand what works for who under what circumstances and why. A point prevalence study of blended diet use in the UK will identify a stratified sample of professionals and families for interviews exploring their experiences. A Delphi study will prioritise key issues identified in the interview data.

**Summary:**

This paper presents a novel, realist mixed methods protocol to investigate the contextual factors influencing the use of blended diets for children and young people across health, education and social care settings in the UK. Grounded in lived-experience, it addresses a critical gap in the evidence-base responding to family-identified priorities. Integrating qualitative and quantitative data enhances explanatory power and applicability to practice. Findings will inform future interventions and policy development, aiming to improve support and equity in blended diet provision. This research offers a robust foundation for advancing personalised enteral feeding approaches within multidisciplinary care.

## Background

Enteral tube feeding is a method of providing nutrition and fluids for children and young people who are unable to take enough food and drinks by mouth and are therefore at risk of malnutrition (NICE, 2006). Underlying conditions such as cerebral palsy, which accounts for a significant proportion of gastrostomy placements in the UK, often result in the inability to manage sufficient oral intake (Popescu and Mutalib, 2023). Enteral tube feeding can be used as a sole source of nutrition for those unable to swallow safely or in addition to an oral diet where supplementary nutrition is necessary.

Enteral tube feeding dates back centuries; however, technological advancements in the 1950s have shaped current enteral tube feeding practices (Harkness, 2002). During this period, enteral tube feeding was used most during periods of acute illness in hospital settings. More recently, the use of home enteral tube feeding has increased significantly as children and young people are living longer with complex medical needs necessitating long term enteral tube feeding outside of a hospital environment. Many of these individuals have life-long conditions, in contrast to acute illnesses, and require support from carers and other health and care services. Although the feeding methods itself does not differ, community settings present distinct priorities and challenges.

Guidelines in the UK advise using a commercial formula for enteral tube feeding (NICE, 2006). Commercial formulas are ready-made, liquid formulas available on prescription in the UK. They are nutritionally complete in a specified volume and can be given as a bolus or using a pump. However, increasingly individuals and their families are choosing to use blended diets and reporting an array of benefits associated with this practice (Breaks et al., 2018; McCormack et al., 2023). A blended diet consists of everyday foods blended to a puree in addition or as an alternative to commercial formula (Durnan et al., 2021). Blended diets are most commonly used with gastrostomy tubes which are therefore the focus in this study; current guidance cautions against using them with nasogastric and post-pyloric tubes (Durnan et al., 2021). Families report benefits such as reduced gastrointestinal symptoms and greater inclusion in family mealtimes. In addition, families of children with complex needs highly value the normalisation of gastrostomy feeding (Durnan, 2018; Phillips and Coad, 2023).

Families often choose blended diets because commercial formula is poorly tolerated which highlights the need for alternatives (Phillips and Coad, 2023). Families report a ‘radical change’ after commencing a blended diet although a lack of support to use them (Durnan, 2018). This ‘radical change’ was associated with reduced reflux and vomiting, healthy growth and improved wellbeing. Some studies have associated the use of a blended diet with improvement (95%) in gastrointestinal symptoms (Batsis et al., 2020) whilst others have demonstrated a reduction (39%) in those using medications to manage these symptoms following transition to a blended diet (Kernizan et al., 2020). Although the mechanisms remain unclear, some authors hypothesise that changes in the gut microbiome as a result of a blended diet may contribute to these changes (Marchesi et al., 2022). This is pertinent to children and young people whose gut flora may lack diversity due to extensive enteral tube feeding from an early age (Marchesi et al., 2022). These changes to the gut microbiome may also improve general health and wellbeing (Gallagher et al., 2018). In addition, blended diets have also been shown to reduce the frequency of respiratory infections and access to acute healthcare facilities which are common amongst individuals with neurodisability (Hron et al., 2019).

Furthermore, the impact of using blended diets on the wider family can be significant. Parents report feeling empowered, and value the normalisation of gastrostomy tube feeding associated with using a blended diet (Soscia et al., 2021). Normalisation is particularly important given the complexity of the needs of many of these individuals and the duration of enteral tube feeding which for some may be life-long. Non-oral feeding has been shown to have significant impact on relationships between mothers and their children (Wilken, 2012). This sense of loss associated with enteral tube feeding is a key factor influencing parents/carers’ decision to use a blended diet for their child (Breaks et al., 2022).

Nutritional inadequacy and tube blockage are common concerns related to using blended diets. However, studies show that adverse events happen less frequently and are less problematic than anticipated (Armstrong et al., 2017). The protein and fat content of blends have been shown to be comparable to commercial formula with blended diets offering greater fibre content (Gallagher et al., 2018; Ojo et al., 2020). Nutritional deficiencies can occur with both commercial formula and blended diets with professional oversight shown to mitigate this risk (Breaks et al., 2018; Schultz and Kim, 2024). In addition, parents/carers report greater satisfaction with support from professionals as opposed to social groups (Staunton et al., 2023).

Current British Dietetic Association guidance now encourages open discussions with families and the multidisciplinary team about blended diets to support informed decision making (Durnan et al., 2021). Previously, blended diets were actively advised against, and early re-emergence was met with caution. Despite updated guidance, families continue to encounter barriers when using blended diets (Armstrong et al., 2017). Studies show that resistance from health and social care professionals towards blended diets remains (Phillips et al., 2024). Whilst guidance suggests that dietitians should lead multi-professional discussions around blended diets, only 35% (n = 51) of dietitians in a study by O'Connor et al. (2025) reported feeling confident or very confident to review a child using a blended diet. Certain organisations continue to prohibit blended diets and families feel frustrated by this lack of support with many ‘forced to compromise’ (Breaks et al., 2018). Anecdotal evidence suggests that support for blended diets varies across the UK, resulting in inequitable service provision.

There is little published research relating to the use of blended diets being used in health, education and social care settings. The increased use in the UK has been driven by families as opposed to being introduced in the same way as other healthcare interventions through design, development and rigorous testing using randomised trials. The majority of the current evidence is observational which limits certainty of causation. However, choices about enteral tube feeding for children and young people, many with additional needs, are complex. Consequently, it is unlikely that a single method of feeding is superior which challenges the concept of a ‘gold standard’. Therefore, options are necessary so that feeding practices can be personalised to individual children, young people and their families and they are supported to make informed choices. Research on blended diets must therefore consider this complexity.

Patients and families using blended diets also report a range of benefits including symptom relief and social inclusion. The increase in the use of blended diets is largely driven by families seeking an alternative to commercial formula for their tube-fed child. These families continue to receive insufficient support across these settings which directly informed the development of this study.

In summary, blended diets are becoming increasingly common and they have the potential to improve health and quality of life for patients and their families. Research has demonstrated positive patient, carer and family experiences in the absence of consistent support which can be problematic. This study builds on other recent work in the field exploring health outcomes, resource implications, benefits and complications of blended diets for gastrostomy feeding (Fraser et al., 2024; McCormack et al., 2023).

The proposed study focuses on the implementation of blended diets and comprises the early stages of complex intervention development to optimise the support families receive to use blended diets. Complex interventions are required for complex health and social problems and often have multiple interacting components which operate in dynamic situations. Complex intervention development consists of four stages: identification, feasibility, evaluation and implementation (Skivington et al., 2021). The identification stage focuses on understanding as a foundation for subsequent development. An understanding the wider context is key to developing effective interventions in health and social care and applies to all disciplines. This study is distinctive in its approach to encompass health, education and social care services aligning to government strategy to embed integrated care systems and coordinate services (Bliss et al., 2024). This is pertinent to children and young people with complex care needs as it is likely that they access a multitude of services across health and social care. Families report that segregation between services, health and social care can hinder holistic care for their child or young person impacting the whole family.

## Aim

To explore factors affecting the use of blended diets for children and young people in health, education and social care settings in the UK.

Objectives:
Identify the prevalence of the use of blended diets for children and young people across the UK.Explore views and experiences of health, education and social care professionals and families to determine the context and underlying mechanisms affecting the use of blended diets.Identify and prioritise components of an intervention to support the delivery of blended diets in health, education and social care settings.

## Methods

This sequential mixed methods study follows a realist evaluation approach outlined by Pawson and Tilley (1997). It is a theory-driven approach which moves beyond evaluating effectiveness to explore how contextual factors trigger mechanisms to generate outcomes. The approach is grounded in critical realism which assumes a stratified reality influenced by social structures (Bhaskar, 1975). Critical realism accepts the complexity of influential social structures in these contexts which is common in health and social care and provides a lens to examine what works through the study of causal mechanisms (Koopmans and Schiller, 2022; Williams et al., 2017). Whilst randomised controlled trials are a highly valued method in healthcare research for attributing causation, realism challenges the lack of external validity in such studies (Emmel et al., 2018; Wallace et al., 2022). Interventions such as blended diets cannot be blinded to increase validity of randomised studies and require observation within their context hence a realist stance is suited to this research.

The generation of context, mechanism and outcome configurations (CMOCs) is central to realist research to generate and refine a programme theory (Pawson and Tilley, 1997). In this study, initial programme theory will be generated by the researcher and key stakeholders with reference to the evidence-base. The Non-adoption, Abandonment, Scale-up, Spread and Sustainability (NASSS) framework (Greenhalgh et al., 2017) will be used to ensure wider influences are considered. This provides an overarching framework to situate the study and the influences on the use of blended diets (see Figure 1).

**Figure 1. fig1-02601060261439096:**
[figure not shown]
The non-adaption, abandonment, scale-up spread and sustainability (NASSS) framework (Greenhalgh et al., 2017). Source: ©Trisha Greenhalgh, Joseph Wherton, Chrysanthi Papoutsi, Jennifer Lynch, Gemma Hughes, Christine A'Court, Susan Hinder, Nick Fahy, Rob Procter, Sara Shaw. Originally published in the Journal of Medical Internet Research (http://www.jmir.org), 01.11.2017.

### Study design

This study uses a sequential mixed methods design consisting of three work packages to achieve the study aim (see Figure 2). Quantitative data will demonstrate the scale of blended diet use whilst qualitative methods will capture the voice of families and professionals with experience of blended diets to meet the study objectives. This will provide a rich understanding of mechanisms at play and influential contexts. Previous research and PPIE has highlighted that families have significant expertise due to the role of families in raising the profile of blended diets.

**Figure 2. fig2-02601060261439096:**
[figure not shown]
Mixed methods study design.

Integration is key to mixed methods studies whereby both methods ‘are in dialogue’ (Plano Clark, 2019) with each other. In this study, findings from the point prevalence study (work package 1) will inform the sampling of participants for the interview study (work package 2). Participants for the interview study (work package 2) will be recruited through NHS organisations with high prevalence of blended diet use. This will support rich data collection about the contexts and mechanisms supporting their use. Initial rounds of the Delphi study (work package 3) will be informed by the interview data so that contextual factors and influential mechanisms identified can be ranked and prioritised ahead of subsequent stages of intervention development.

Mixed methods studies are suited to understanding complex phenomena which cannot be adequately explored using qualitative or quantitative methods alone (Plano Clark, 2017). Mixed methods research supports an understanding of ‘how’ and ‘why’ rather than simply ‘what’ which is key in this research which is complex and nuanced. The aim of using mixed methods in this study is to establish generative causation, necessary for realist research; quantitative methods can identify patterns whilst qualitative insights identify the causal mechanisms.

A Good Reporting of a Mixed Methods Study (GRAMMS) checklist can be seen in Appendix 1 (O'Cathain et al., 2008).

### Participants

Families of children and young people using enteral feeding tubes are the focus of this research. The study focuses on the provision of enteral tube feeds which is predominantly a parental responsibility; hence, participants will be adults (parents/carers) or young people (over 16 years) if they manage their own enteral tube feeding. The complexity of these children and young people means that they rely on parents or carers much more than others their age. Consequently, their health and care needs can have a huge impact on the whole family. In this study, the definition of children and young people includes those up to 25 years old in line with government legislation related to special educational needs and disabilities which are common in this group (Department for Education and Health, 2015).

The study will use the following inclusion and exclusion criteria:

#### Work package 1

Inclusion:
National Health Service provider in the UK

Exclusion:
Health service providers known to not be involved in home enteral tube feeding (e.g. ambulance trusts)

#### Work packages 2 and 3

Inclusion:
Parent or main carer of a child or young person (aged 0–25 years) or young person aged 16–25 years using home enteral tube feeding in the UK.Professionals who work for an organisation within health, education or social care in the UK providing services to children and young people using home enteral tube feeding.Interview study only: Access or work within organisations associated with NHS Trusts identified in point prevalence study.

### Sampling and recruitment

All NHS organisations will be considered for inclusion in the point prevalence study which will identify the number of people using home enteral tube feeding and of those, the proportion using a blended diet. They will be contacted using freedom of information act requests to obtain data on prevalence of home enteral tube feeding and use of blended diets.

Purposive sampling for the interview and Delphi study will ensure that participants have the relevant knowledge, experience and expertise of blended diets necessary to gather rich, in-depth data (Palinkas et al., 2015). Participants will be recruited through NHS trusts and health boards and other organisations such as special needs schools and hospices to achieve a diverse sample. Eligibility criteria for the interview and Delphi study are the same, and participants can partake in one or both. Additional participants may also be recruited using a snowballing method. Authors acknowledge that participants included in the study may have experienced different or fewer barriers to families without awareness or experience of blended diets. However, an understanding of ways that barriers have been overcome was deemed an insightful first step in developing knowledge on the topic.

A sampling framework will be used to capture those with a range of experience (length of time using a blended diet or professional background). The framework provides an approximate sample size and may be adjusted according to the conceptual depth of the data collected (see Appendix 2). Multi-disciplinary Delphi panels need to be larger to capture a range of participants as is the case with this study (Manyara et al., 2024). In addition, PPIE representatives have explained that due to the fluctuating care needs of their children, their availability to partake may vary. For this reason, a larger panel may be necessary to accommodate a higher than usual drop-out rate. It is generally advised to seek a minimum panel size and ensure representation of subgroups (Beiderbeck et al., 2021; Page et al., 2015).

Participants will contact the researcher if they would like to take part in the study. They will be sent a participant information sheet and an expression of interest form to complete. This will include demographic information, contact details and criteria required to assess suitability based on the sampling framework in addition to any communication needs that need to be accommodated by the researcher. Eligible participants will then be contacted by the researcher to agree participation and complete the consent process.

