### Data analysis

The point prevalence of blended diet use will be calculated for each organisation and descriptive statistics (e.g. mean, median) will be calculated for the whole data set as well as separately for children (0–17 years) and young people (18–25 years).

Reflexive thematic analysis will be used for the interview study (Braun and Clarke, 2019). This supports a realist approach to offering an explanatory understanding of the context and mechanisms affecting the use of blended diets recognising the co-creation of knowledge between the researcher and the data. A proportion of the interview recordings will be transcribed by the researcher to aid familiarisation; any transcribed externally will be read multiple times. Interview transcripts will be coded by the researcher by identifying meaningful words and phrases. Codes will then be grouped into themes and labelled to summarise important topics in the data collected.

Coded data will also be used to refine the programme theory. Data will provide evidence to confirm, refine or refute the programme theory through an iterative process involving stakeholders and patients and members of the public. Causal mechanisms and their influence on outcomes of interest will be explained using CMOCs.

Data analysis in the Delphi study will involve calculating frequencies of responses, medians and interquartile range of Likert scales. Qualitative data from free text responses will be analysed using reflexive thematic analysis as with the interview data. Response rates, drop-outs and characteristics of the panel will be monitored and reported in the study findings. Data from the Delphi study will be used to further refine the programme theory through iterations of the CMOCs.

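### The prevalence denominator covers all home enteral tube feeding, while the stated focus is gastrostomy, so uptake in the focus group may be understated and site selection depends partly on tube mix

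*Protocol article*

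**What the plan says.** The Background states the scope: "Blended diets are most commonly used with gastrostomy tubes which are therefore the focus in this study". It adds that "current guidance cautions against using them with nasogastric and post-pyloric tubes".

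The first objective, under Aim, is to "Identify the prevalence of the use of blended diets for children and young people across the UK". Under Sampling and recruitment, the prevalence study will "identify the number of people using home enteral tube feeding and of those, the proportion using a blended diet", and NHS organisations will be approached by freedom of information request "to obtain data on prevalence of home enteral tube feeding and use of blended diets". Neither sentence mentions tube type.

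The Data analysis section calculates one point prevalence per organisation, then summarises it overall and "separately for children (0–17 years) and young people (18–25 years"). There is no stratum for tube type.

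Under Participants, work package 1 is defined at provider level. The family criteria for work packages 2 and 3 cover a parent or main carer of someone aged 0–25, or a "young person aged 16–25 years using home enteral tube feeding in the UK". Gastrostomy is not a criterion in any work package.

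Under Study design, the interview participants are to come through NHS organisations where blended diet use is high, so the prevalence figure also serves to choose sites.

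**The concern.** The gastrostomy focus does not reach the measurement. On the article's own account, the denominator includes people with tubes for which guidance urges caution about the very practice being counted. The prevalence has two uses, and both are affected.

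First, it answers the prevalence objective. If use is lower with other tubes, the all-tube proportion is lower than uptake in the group the article says it is about.

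Second, it steers the interviews. Two organisations that support gastrostomy families equally well will record different prevalence if one has a larger nasogastric or post-pyloric caseload. The interviews are meant to find the contexts and mechanisms that support blended diets, and their findings feed the Delphi rounds. A supportive organisation left out because of its caseload is lost to both later stages.

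**Working it through.** The article states no expected prevalence, tube mix or sample size for this work package, so there is no figure to reproduce. The check has two parts: a comparison of the text, and an illustration on assumed values.

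**Text, element by element**

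| Element | Background | Participants (work packages 2 and 3) | Sampling and recruitment | Data analysis |
|---|---|---|---|---|
| Tube type | Gastrostomy is the focus | Any home enteral tube feeding | Any home enteral tube feeding | No stratum |
| Age | Not limited here | 0–25 | Not stated in the sentence | 0–17 and 18–25 |

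Tube type differs between the Background and the three operative sections. Age does not conflict: the objective, the definition and the analysis bands agree on 0–25.

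**Illustration**

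Let g be the gastrostomy share of those on home enteral tube feeding, b the proportion of gastrostomy users on a blended diet, and o the proportion among users of other tubes. Then:

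recorded prevalence = g × b + (1 − g) × o

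All three inputs are assumptions.

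*Dilution, b = 20%:*

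| g | o = 0 | o = 2% |
|---|---|---|
| 0.4 | 0.4 × 20% = 8% | 8% + 0.6 × 2% = 9.2% |
| 0.6 | 0.6 × 20% = 12% | 12% + 0.4 × 2% = 12.8% |
| 0.8 | 0.8 × 20% = 16% | 16% + 0.2 × 2% = 16.4% |
| 0.9 | 0.9 × 20% = 18% | 18% + 0.1 × 2% = 18.2% |

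With o = 0 the recorded figure is simply g times the gastrostomy figure, that is 40% to 90% of it over this range.

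*Same practice, different record:* two sites with b = 20% and o = 0, one with g = 0.6 and one with g = 0.9, record 12% and 18%, a ratio of 1.5 that comes from caseload alone.

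*Order reversed (o = 0):*
- Site A: b = 25%, g = 0.5, recorded 0.5 × 25% = 12.5%.
- Site B: b = 18%, g = 0.9, recorded 0.9 × 18% = 16.2%.

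Site A has the higher uptake among gastrostomy users but the lower recorded figure. With a gastrostomy denominator the two would show 25% and 18%.

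*Direction of the selection error:* whenever o is no greater than b, g × b + (1 − g) × o cannot exceed b. A site that looks high therefore has gastrostomy uptake at least that high. The risk is mainly one of overlooking suitable sites, not of choosing low-use ones.

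**The case against.** The strongest reply is that the Background names a focus and sets no eligibility rule. It says blended diets are mostly, not only, used with gastrostomy, and that guidance is cautious about other tubes, not that it forbids them. The Participants section describes its population as families of tube-fed children and young people in general, and the denominator matches that population and the first objective. Blended diet use among all tube-fed children and young people is a legitimate descriptive quantity. This stands, and it means the all-tube figure should be kept. It does not remove the mismatch with the stated focus or the dependence of site selection on tube mix.

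The harm to the interviews is also limited. Sampling is purposive, uses a framework based on experience, includes schools and hospices and allows snowballing. The analysis of prevalence is descriptive, and no test between sites rests on it. This stands too, and it bears on how serious the point is.

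The request form is not shown and might already ask for tube type. That is possible, but the denominator and strata that the article does state make no use of it.

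A reader might also infer from the word people under Sampling and recruitment that adults over 25 enter the denominator. The documents do not support this. The objective concerns children and young people, the Participants section says "the definition of children and young people includes those up to 25 years old", and the two analysis bands together make up exactly 0–25. At most the wording is loose.

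**Conclusion.** The point holds for tube type. The article declares a gastrostomy focus but fixes a denominator of all home enteral tube feeding and plans no split by tube. If use is lower with other tubes, the planned figure understates uptake among gastrostomy users, and selection for high prevalence can pass over supportive sites with many non-gastrostomy patients.

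The size cannot be derived from the documents. The figures in the working show the mechanism on assumed values and measure nothing in this study. If tube mix is much the same everywhere, the level is still diluted but the order of sites is little affected. It would be tempting to conclude that low-use sites will be chosen or that the study is restricted to gastrostomy; neither follows from the text.

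This is a consistency defect of modest consequence. It should be settled before the requests go out, because counts by tube type that were not asked for would need a second national round of requests.

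**What to change.** In the freedom of information request, ask each organisation, separately for ages 0–17 and 18–25, for:

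1. the number on home enteral tube feeding;
2. the number of those with a gastrostomy;
3. the number using a blended diet in total;
4. the number using a blended diet among those with a gastrostomy.

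Report (4)/(2) as the prevalence for the stated focus and use it to select interview sites. Report (3)/(1) alongside it for every organisation.

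Where tube type is not held, report only (3)/(1), and compare those organisations with others on that figure alone. The two denominators must never be compared with each other: at b = 20%, g = 0.6 and o = 0, a site without tube data would show 12% against 20% for a site with identical gastrostomy practice that does hold them.

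Reconcile the gastrostomy focus in the Background with the wider criteria under Participants, either by aligning them or by stating that the criteria are deliberately wider. Withdrawing the focus would settle the wording but leave site selection dependent on tube mix. Under Sampling and recruitment, state ages 0–25 in place of people.

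The cost is a slightly longer request, and some organisations may not hold tube type. The planned pilot on 5% of sites, with changes as needed, is the natural place to find out how many do.
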